#### SWAP

The SWAP aims to explore uptake of and engagement with HEAL-D in adults with T2D who also have MLTC, and has the following objectives: (1) to assess the prevalence of MLTC in adults of Black African or Black Caribbean ethnicity participating in the HEAL-D trial and identify and describe common MLTC clusters; (2) to assess the impact of MLTC on uptake, engagement with, and completion of HEAL-D; (3) to assess the impact of the HEAL-D intervention on associated MLTC; and (4) to codevelop dissemination outputs in a workshop with a patient and public involvement and engagement (PPIE) group and other relevant stakeholders, ensuring strong representation of those with MLTC. The SWAP will be conducted in two phases: quantitative data collection, to address objective 1, and qualitative data collection to address objectives 2-4. All participants will be eligible for the SWAP and have quantitative data collected (eg, prevalence and details of MTLC); only participants randomized to the intervention arm will be eligible to participate in the qualitative data phase (ie, semistructured interviews and workshops).

All study participants will complete a questionnaire to elicit background information on the long-term conditions they experience (with MLTC defined as per Guthrie et al [62]). The extent to which these conditions affect their day-to-day living will be assessed using the Multimorbidity Treatment Burden Questionnaire. This questionnaire will be analyzed together with participant demographic data and baseline exercise capacity, QoL, and psychological assessments. A subsample of participants who are randomized to the HEAL-D arm will undertake an interview focusing on: experience of T2D, experience of MLTC, uptake of and engagement with the HEAL-D intervention (both F2F and remote attendance), trial experience, trial completion, and interaction between MLTC and intervention. These interviews will be embedded in the process evaluation and account for 16/48 of the participant interviews. Qualitative data will also be obtained within the three main process evaluation workshops, where additional needs of people with MLTC, the burden of MLTC, and barriers and facilitators to acceptance of HEAL-D will be discussed. For the SWAP, there will also be two additional workshops to deliberate on whether the intervention could be optimized for MLTC and what lessons can be shared with other stakeholders going forward.

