**Tertiary or exploratory outcomes**						
	Blood lipids					
		LDL^k^-cholesterol (mmol/L); nonfasting blood sample	✓	✓	✓	✓
		Triglyceride (mmol/L); nonfasting blood sample	✓	✓	✓	✓
	Body composition: body fat (kg and %); measured using bioelectrical impedance analysis		✓	✓	✓	✓
	Lifestyle behaviors: self-reported sleep duration and chronotype		✓	✓	✓	✓
	Medication use					
		Glucose-lowering therapies use, assessed via self-reported medication history	✓	✓	✓	✓
		Blood pressure-lowering therapies use, assessed via self-reported medication history	✓	✓	✓	✓
	Multimorbidity status					
		Diagnoses or remission or changes in severity of medical conditions, assessed via self-reported medical history	✓	✓	✓	✓
		MTBQ^l^	✓	✓	✓	✓

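### The SWAP assigns its two impact objectives to qualitative work in the HEAL-D arm alone and does not use the scheduled quantitative data that could estimate them

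*Protocol article*

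**What the plan says.** The SWAP section lists four objectives. The second is "to assess the impact of MLTC on uptake, engagement with, and completion of HEAL-D" and the third is "to assess the impact of the HEAL-D intervention on associated MLTC". It then fixes the method for each: "quantitative data collection, to address objective 1, and qualitative data collection to address objectives 2-4". All participants give quantitative MLTC data, but "only participants randomized to the intervention arm will be eligible to participate in the qualitative data phase". That phase consists of interviews, which "account for 16/48 of the participant interviews", together with the three main process evaluation workshops and two further SWAP workshops.

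Elsewhere the article schedules the relevant data. Table 1, under tertiary or exploratory outcomes, lists "Diagnoses or remission or changes in severity of medical conditions, assessed via self-reported medical history" and the MTBQ, each at baseline, 6, 12 and 24 months. Secondary and Exploratory Outcomes names change in MLTC status as a tertiary outcome. Mixed Methods Process Evaluation counts attendance and completion rates as intervention dose.

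The SWAP section also plans to analyze the questionnaire data with "baseline exercise capacity, QoL, and psychological assessments".

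**The concern.** Objective 3 asks for the effect of a randomized intervention. Answered only from accounts given by HEAL-D participants, it has no comparator, so an effect of HEAL-D cannot be told apart from the passage of time, usual care or the selection of interviewees.

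Objective 2 asks how one characteristic relates to uptake and completion. It properly concerns the HEAL-D arm only, but qualitative material gives no estimate of that relation. The sampling adds to this: process evaluation participants are chosen for diversity in both engagement and MLTC status. Their joint distribution among interviewees is therefore set by design and does not reflect the trial population.

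Both questions appear in the Abstract, Aims and Study Design as things the trial will assess, and Aims places them under a mixed methods evaluation. If the SWAP section is followed literally, the report will offer perceptions where readers expect estimates, although the data for estimates will have been collected.

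**Working it through.** **1. The plan's own figures.** The SWAP states no power or precision, so the only figure to reproduce is the arm size in Sample Size Calculation (difference 5, SD 11 mmol/mol, 90% power, 5% two-sided).
- Normal approximation: 2 × (1.960 + 1.282)² × (11/5)² ≈ 101.7, so 102 per arm. The t-test version gives 102.7, so 103, as stated.
- Design effect: 1 + (10 − 1) × 0.01 = 1.09. Then 103 × 1.09 = 112.3, or 120 in whole groups of 10.
- Loss of 15%: 120 / 0.85 = 141.2, or 150 in whole groups.

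The arm size is sound and is not in dispute.

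**2. Objective against method.**

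| Objective | What it needs | What the SWAP section assigns | What the trial already schedules |
|---|---|---|---|
| 2 | Uptake and completion by MLTC status in the HEAL-D arm | Interviews and workshops | Baseline MLTC; HEAL-D attendance and completion |
| 3 | Between-arm contrast in MLTC change | Interviews and workshops, HEAL-D arm only | MLTC status and MTBQ in both arms at four timepoints |

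The SWAP interviews cover 16/150 = 10.7% of the HEAL-D arm and no controls. Interviews take place within 1 month of the 12-month visit, so they cannot speak to months 12-24.

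**3. What the scheduled data would give for objective 3.** Take a continuous score such as the MTBQ, 15% loss (150 × 0.85 = 127.5, taken as 127 per arm) and a design effect of 1.09 in the HEAL-D arm only.
- SE in SD units: √(1.09/127 + 1/127) = 0.128.
- 95% CI half-width: 1.96 × 0.128 ≈ 0.25 SD.
- Detectable difference: (1.960 + 0.842) × 0.128 ≈ 0.36 SD at 80% power; (1.960 + 1.282) × 0.128 ≈ 0.42 SD at 90%.
- The ICC of 0.01 was chosen for HbA1c. If it were 0.05 for this score, the half-width would be 0.27 SD and the 80% detectable difference 0.39 SD.

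These figures take no credit for baseline adjustment. The 15% loss is the plan's 12-month figure; loss at 24 months may be larger.

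**4. What the scheduled data would give for objective 2.** Difference in completion by MLTC status among 150 HEAL-D participants; half-width = 1.96 × √[p(1 − p)(1/a + 1/b)]. MLTC prevalence and completion p are assumptions.

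| MLTC split (a, b) | p = 50% | p = 60% |
|---|---|---|
| 75, 75 | 16.0 points | 15.7 points |
| 45, 105 (prevalence 30% or 70%) | 17.5 points | 17.1 points |

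The half-width is thus about 16 to 17 points, before any allowance for group.

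**5. Exercise capacity.** Neither Table 1 nor Measurements contains an exercise capacity test. The baseline activity measures are accelerometry and the s-IPAQ, which record activity, not capacity.

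**The case against.** The strongest reply is that the trial does hold a randomized answer to objective 3. Change in MLTC status is a tertiary outcome of a two-arm trial, and models for tertiary outcomes are commonly left to an analysis plan, which is not shown here. This stands, and it limits the point. A reader might infer that the impact of HEAL-D on MLTC cannot be answered by this trial. The documents do not support that: the data are scheduled in both arms, and a comparison may be planned elsewhere. What remains is that the SWAP section expressly assigns the objective to another method and does not link it to the tertiary outcome.

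A reader might also infer that objective 2 is flawed for want of controls, or that both arms supply equivalent attendance data. Neither follows. Controls are not offered HEAL-D, so the HEAL-D arm is the right population. For controls, the article states only time to attendance and engagement with allocation.

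Third, qualitative inquiry into how MLTC affects engagement is legitimate. The SWAP aims to explore, it includes workshops as well as interviews, and the process evaluation triangulates qualitative with quantitative data. All of this supports keeping the qualitative work. It does not turn that work into an estimate, and the triangulation as described includes no between-arm MLTC comparison and no model of engagement on MLTC.

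**Conclusion.** The point holds as a mismatch between objective and method in the SWAP section. Objectives 2 and 3 are worded as impact questions but assigned to material from the HEAL-D arm that can describe perceived impact and cannot estimate it. The scheduled data could support a between-arm contrast to about ±0.25 SD on a continuous score (15% loss, ICC 0.01), and a completion difference by MLTC status to about ±16 to 17 points (assumed MLTC prevalence 30-70%, completion 50-60%).

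The consequence is modest. These are exploratory questions in an embedded study and do not touch the primary result. Two limits would remain after the change: MLTC status and MTBQ are self-reported in an open-label trial, so randomization supplies a comparator but does not remove reporting bias; and MLTC is not randomized, so objective 2 yields an association and not a causal effect. The exercise capacity wording is a minor mismatch and adds no weight to the main point.

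**What to change.** Amend the SWAP section as follows.

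- **Objective 3:** answer it by the randomized comparison of MTBQ and change in MLTC status at 6, 12 and 24 months. Use the repeated-measures mixed model that Statistical Analysis already sets out for secondary outcomes, with its group effect, and a logistic version for new diagnosis or remission.
- **Objective 2:** regress uptake, attendance and completion on baseline MLTC within the 150 HEAL-D participants, adjusting for center and allowing for group where relevant (participants who never attend have no group attended).
- **Status:** label both analyses exploratory, report estimates with confidence intervals, and keep interviews and workshops to explain them.
- **Wording:** replace baseline exercise capacity by baseline accelerometry or s-IPAQ.

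The cost is a few lines of text and a small amount of exploratory analysis with limited precision. No new data collection is needed. The change should be made before follow-up MLTC data are examined by arm.

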### Sample Size Calculation

The trial is based on a minimal clinically important difference in HbA_1c_ of 5 mmol/mol, leading to significant risk reductions for T2D complications [19]. Power was calculated at 90%, with a 5% 2-sided significance level, to detect a standardized effect size of 0.45 (difference in HbA_1c_ of 5 and SD of 11 mmol/mol, determined from the feasibility trial [34] and unpublished primary care data from South London). To allow for correlation of outcomes among group attendees, the sample size, assuming no correlation (103 per arm), is inflated by a design effect (1.09) and then rounded up to ensure divisibility by group size. The F2F intervention is to be delivered in groups of up to 12, while the remote intervention will be delivered in groups of up to 8; for the calculations, an average group size of 10 is assumed. Given the objective outcome, the short duration of treatment, patterns observed in the intracluster correlation coefficient for cluster randomized trials suggest an intracluster correlation coefficient of 0.01 [63]. In the previous feasibility trial, loss to follow-up was 7% at 6 months. Given the pragmatic design, whereby participants are given free choice as to their mode of attendance (F2F or remote) in both the intervention and comparator arms, we do not expect substantial differences in retention between arms. However, with a longer primary outcome follow-up of 12 months, loss to follow-up is estimated to be higher at 15%. For the intervention arm, this is accounted for by increasing the number of clusters. Therefore, we will recruit 150 participants in the control arm and 150 participants in the intervention arm, each across 15 groups of average size 10.

### Statistical Analysis

Primary analysis of change in HbA_1c_ at 12 months will be conducted using a mixed effects model with a random effect for the group attended; individuals in the control arm will be treated as groups of size 1 [64]. Treatment arm, center, and baseline HbA_1c_ will be included as fixed effects. The primary analysis will be repeated to include an interaction term between treatment and mode of delivery (F2F or remote) to explore any differential treatment effect among groups. The presence of an interaction will be tested using a likelihood ratio test. The prespecified subgroup analyses of the primary outcome will assess whether the effectiveness of the intervention is dependent on baseline HbA_1c_ or center. This will be assessed by adding interaction terms between group allocation and the potential effect modifiers to the linear regression, one at a time. The analysis exploring the change in treatment effect over time for the secondary outcomes will follow the methodology of the primary analysis, with an additional random effect for the individual to account for within-individual correlation over time, a fixed effect for time, and an interaction between treatment and time effect. Mediation analysis will be conducted using multilevel structural equation modeling [65]. To account for missing data, multiple imputation will be undertaken, provided we have strong predictors of missingness and an appropriate imputation model. Diagnostic checks will be performed to assess this. The missing data mechanism will be assumed to be missing at random. Individual analyses on each imputed dataset will be combined using the Rubin rules. Sensitivity analyses will be conducted to assess the robustness of the primary conclusions to the imputation strategy used.

For data collected during the mixed methods process evaluation, deductive and inductive thematic analysis of interviews, workshops, logs, and observations, using NVivo (QSR International) Framework, will be followed by triangulation of qualitative and quantitative data using a meta-matrix [66]. We will examine divergence and similarity across study groups (eg, remote vs F2F, by center), and within the triangulated data to develop a comprehensive understanding of intervention delivery and fidelity, recruitment and engagement, and mechanisms of impact. Thematic analysis [67] will be undertaken with the interview transcripts, informed by the Theoretical Domains Framework and the COM-B framework, toward identifying barriers and facilitators for engagement and maintenance of behavior change [63]. For the thematic analysis, using NVivo software, two researchers will independently double-code 10% of randomly selected transcripts to develop a coding framework. Further transcripts will be double-coded one by one until interrater reliability is such that the framework is agreed upon. Remaining transcripts will then be single-coded (ie, by one of the two researchers). Themes will be developed through discussion with the wider team. To indicate the frequency with which themes occur, we will use “all” (100%), “almost all” (>85%), “most” (>75%), “the majority” (>50%), “some” (>10%), and “a few” (≥10%). We will use the Consolidated Criteria for Reporting Qualitative Research tool [68]. The health economic evaluation analysis has been described in the relevant section.

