### Control Group

Control group participants will be referred to attend the standard NHS-commissioned DSMES course that is delivered in their local area and will be offered the choice of attending F2F or remote delivery, where both delivery methods are available. DSMES courses are a core NHS service with management guidelines recommending that all people with T2D attend a DSMES course [19], and referral is incentivized in primary care [44]. The content and structure of DSMES courses are guided by a quality framework, requiring courses to be group-based, delivering an evidence-based curriculum to support self-management skills, and be delivered by skilled, competent staff [19]. A range of courses are delivered in the NHS, typically providing 6-14 hours of group-based education and support; these courses are typically based on a standardized curriculum that does not include culturally tailored information or advice. HEAL-D has been developed to align with the quality standards for DSMES programs, but it is different from existing NHS courses in several ways. Principally, HEAL-D has been developed through a rigorous co-design process to reflect African and Caribbean cultural health beliefs and practices, providing tailored information, advice, and support through culturally sensitive resources. Furthermore, delivery is led by a combination of healthcare professionals (dietitians), culturally concordant “lay” facilitators, and exercise trainers, and the program includes participatory physical activity classes and practical cooking workshops.

In both trial arms, information on the factors that drove the choice of attendance mode will be collected. Following randomization, participants will attend their allocated DSMES program within 4 weeks, where possible, and the time from randomization to attendance will be recorded.

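### The primary model treats every control as ungrouped, although control DSMES is group-based and, read literally, sized in 15 groups of 10; where controls share courses, the standard error is slightly too small

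*Protocol article*

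**What the plan says.** Three sections of the protocol article bear on this.

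- **Control Group.** Controls are referred to the standard NHS course in their area. The content and structure of these courses are "guided by a quality framework, requiring courses to be group-based", and the section gives a typical 6 to 14 hours of education delivered in groups.
- **Sample Size Calculation.** The per-arm figure, "assuming no correlation (103 per arm), is inflated by a design effect (1.09) and then rounded up to ensure divisibility by group size", allows for correlation among people attending the same group. The conclusion is that "we will recruit 150 participants in the control arm and 150 participants in the intervention arm, each across 15 groups of average size 10", which on its face describes both arms.
- **Statistical Analysis.** The primary model for 12-month change in HbA1c has fixed effects for arm, center and baseline HbA1c, and a "random effect for the group attended; individuals in the control arm will be treated as groups of size 1".

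No section explains why controls may be analysed as independent of one another, for instance because they would be spread thinly over many routine courses.

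**The concern.** Singleton clusters suit a comparator that is not delivered in groups. The comparator here is delivered in groups, and the sample size text, taken at its word, allows for that clustering in both arms. The analysis then allows for it in one arm only.

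What is at stake is the stated precision of the primary result. If several trial controls sit in the same course, their outcomes may be correlated, and the variance of the control mean is larger than the model assumes. The confidence interval is then too narrow and the p-value too small. The fixed effect for center removes differences between centers' programs but not correlation within a course group.

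**Working it through.** **Inputs, all from the Sample Size Calculation**

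- "Power was calculated at 90%, with a 5% 2-sided significance level"
- "standardized effect size of 0.45 (difference in HbA_1c_ of 5 and SD of 11 mmol/mol"
- 103 per arm before clustering, design effect 1.09, ICC 0.01
- Group size: "for the calculations, an average group size of 10 is assumed"
- 15% loss to follow-up at 12 months; 150 per arm recruited

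**Assumptions not in the document:** ICCs of 0.02 and 0.05, used to show a range; and the number of trial controls per course, m_C, varied from 2 to 10. The value 10 is the literal reading of the sample size text.

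**1. The plan's own figure.** A two-sample t-test for a difference of 5 with SD 11 needs 102.7, so 103 per arm. Design effect: 1 + (10 − 1) × 0.01 = 1.09. Then 103 × 1.09 = 112.3, rounded up to 120 (12 groups of 10). With 15% loss, 120 / 0.85 = 141.2, rounded up to 150 (15 groups of 10). The stated sample size reproduces.

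**2. Formula.** With n per arm, the variance of the difference is SD² × (DE_T + DE_C) / n, where DE = 1 + (m − 1) × ICC in each arm. The singleton model sets DE_C = 1. So

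- true SE / modelled SE = √[(DE_T + DE_C) / (DE_T + 1)]
- actual two-sided type I error = 2 × [1 − Φ(1.96 / ratio)]

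SD and n cancel from the ratio.

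**3. The protocol's own case** (150 per arm, groups of 10 in both arms, ICC 0.01)

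- Modelled SE = 11 × √(2.09 / 150) = 1.298
- True SE = 11 × √(2.18 / 150) = 1.326
- Ratio = √(2.18 / 2.09) = 1.021; type I error about 5.5%

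**4. Range** (HEAL-D groups of 10 throughout)

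| ICC | m_C | SE ratio | Type I error |
|---|---|---|---|
| 0.01 | 2 | 1.002 | 5.05% |
| 0.01 | 3 | 1.005 | 5.1% |
| 0.01 | 5 | 1.010 | 5.2% |
| 0.01 | 10 | 1.021 | 5.5% |
| 0.02 (assumed) | 10 | 1.040 | 6.0% |
| 0.05 (assumed) | 2 | 1.010 | 5.2% |
| 0.05 (assumed) | 10 | 1.088 | 7.2% |

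**5. Simulation.** The formula treats the ICC as known. As a check, 4,000 trials per ICC were simulated with 15 groups of 10 in each arm and analysed by REML. At ICC 0.01 the rejection rate under no effect was 5.2% with singleton controls and 4.8% with control groups modelled, a barely visible difference. At ICC 0.05 the singleton model gave a mean SE of 1.41 against an empirical 1.54, and rejected in 8.1% of trials against 5.9% with control groups modelled.

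**6. Power with control groups modelled.** After 15% loss, 150 × 0.85 = 127.5 per arm. At ICC 0.01, SE = 11 × √(2.18 / 127.5) = 1.438 and power = Φ(5 / 1.438 − 1.96) = 93.5%. With singleton controls the SE would be 1.408 and power 94.4%. Modelling control groups therefore costs about one percentage point. Power would still be 91.6% at an assumed ICC of 0.02, and would fall to 85.4% at 0.05.

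**The case against.** **The sample size sentence may be loosely worded.** The group sizes it draws on are those of HEAL-D, and the extra clusters for attrition are mentioned only for the intervention arm. The 150 controls also follow from 1:1 allocation. If the 15 groups were meant for HEAL-D alone, the flaw there is one of wording. A sample size may also be more conservative than the analysis that follows. This is fair, but the inflation is applied to a per-arm figure, and the Control Group section still describes a group-delivered comparator, so a reason for treating controls as independent is missing either way.

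**Trial controls may seldom share a course.** They join routine local courses, at 3 to 5 centers, by either mode where both exist. The Results section reports 72 randomized between August 2024 and 26 March 2025. That is about 36 controls in roughly seven months, or about five a month across the trial. Faster recruitment would raise the number per course, but ten is the extreme case. This stands, and it is why the size must be given as a range.

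**The effect is small at the planned ICC.** This also stands. The larger figures need ICCs that the document does not state.

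**Stronger readings that the document does not support.**

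- A reader might infer that HEAL-D participants who never attend have no group and would drop out of the model, biasing the result toward HEAL-D. The Statistical Analysis section does not exclude them. Data Collection Procedures seeks outcome data from people who missed sessions, and the Figure 1 legend refers to intention-to-treat. How their cluster is coded is ordinary SAP detail, and neither a non-attendance rate nor a direction of bias can be derived from the text.
- A reader might also infer that the subgroup tests carry no group effect, because they are run by "adding interaction terms between group allocation and the potential effect modifiers to the linear regression, one at a time". The regression meant is most naturally the mixed model described just before.

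**Conclusion.** The point holds as an inconsistency to be reconciled, with a modest statistical consequence. The stated primary model omits control-arm clustering that the protocol, read literally, builds into its own sample size.

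It would be too strong to say flatly that the standard error is too small. That depends on how many trial controls share a course, which the document does not settle. If controls sit in groups of 10 at the planned ICC of 0.01, the true standard error is 2.1% larger than modelled and the type I error is about 5.5%. At about two controls per course there is no practical effect. A type I error of 6% to 7% needs both groups of about 10 and an ICC of 0.02 to 0.05, which is assumed here. The calculation takes the same ICC in both arms. It does not imply that the trial is underpowered at the planned ICC.

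**What to change.** Record the DSMES course group, identified by provider and start date, for each control. In the primary mixed model, use the actual course group as the cluster in both arms, and keep singletons only for participants who share no group with another trial participant.

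Then make the Sample Size Calculation agree with the Statistical Analysis section. If the 15 groups were meant for HEAL-D only, correct that sentence, state that controls are expected to be dispersed over routine courses, and add a sensitivity analysis by actual control course. The course identifier is needed on either route.

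The cost is one data field, a few words of model specification and slightly less favourable precision. No extra participants are needed at the planned ICC, because 150 per arm already carries the 1.09 design effect. With 72 randomized at the time of the article and analysis expected from July 2027, the field is easier to add now than to reconstruct later.
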